#### Recruitment

GPs will be recruited by identified clinicians working to promote continuing medical education in Tunis and Sousse. A training on the description of the study and participant requirements will be given to the identified clinicians before recruitment phase. Identified clinicians will then collect the names and contact information of the interested participants, who will be contacted by JS to obtain written consent before randomization.

### Assignment of interventions

#### Allocation sequence generation

A randomization scheme must be generated to randomize the delegations either to the intervention or control group. Using SAS software version 9.3, a random seed (*blockrand* function) will be used to produce simple randomization by fixed blocks of 3. A list of these simple blocks will be used to determine the delegation assignment.

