### Participants, interventions and outcomes

#### Study setting

To assess the potential value of capacity building by training GPs in Tunis and Sousse using an adaptation of the mhGAP-IG (version 1.0), a cluster randomized controlled trial (RCT) with two arms (i.e., intervention and control) will be conducted. Tunis and Sousse have been chosen as they regroup the majority of the Tunisian population; they have access to the only standing mental health hospital in the country, as well as psychiatric units located in general hospitals; and in this area, there are substantially more resources allocated to mental healthcare (i.e., doctors, clinics, medication) than in other areas of Tunisia. Delegations (i.e., designated areas within the governorates) have been chosen as the clusters for this trial, seeing as health services are organized accordingly in Tunisia. There are 22 delegations in Tunis and 16 in Sousse, for a total of 38 delegations.

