#### Sample size

This trial will answer a number of important questions regarding study design, namely: What is the estimated effect size and ICC of a mental health training based on the mhGAP-IG? These parameters, to our knowledge, were not available at the time this protocol was written and defended (June 2015), and will thus make significant contribution to knowledge on the mhGAP-IG.

Following consultation with members of the Ministry of Health in Tunisia, the recommended average number of GPs to be recruited in the cluster (i.e., the delegation, many of which comprise the governorate) was suggested to be 15. While some studies using a cluster RCT to evaluate the effectiveness of a mental health training program offered to GPs in HICs do not report attrition [49–51], we are concerned that the evidence does not reflect the sampling realities in LMICs. For this reason, we aim to recruit 19 GPs per delegation, to be sure we account for a maximum of 20% attrition rate per cluster [52, 53]. Table 1 highlights the estimated sample size and number of clusters for the trial.

**Table 1 Tab1:** The sample size and number of clusters in the trial

PARAMETERS	#
n (total number of GPs)	722
# clusters (delegation)	38
n cluster (GPs on average per cluster)	19

Using the statistical software G*Power 3.1, the effect size can be calculated after data collection. Parameters will be set at: 1) test family: *t* test; 2) statistical test: difference between two independent means; 3) tail(s): two-tailed test; 4) type of power analysis: sensitivity; 5) alpha: 0.05; 6) power: 0.80; and 7) sample size (i.e., the total number of GPs) for control and intervention groups used in this trial. Once the effect size is found, the estimated ICC can be generated using the following formula, designed for cluster RCTs: *N =* N_sg_ (1 + (m-1) ICC), where:
*N =* number of participants in the trial (i.e., the total number of GPs);N_sg_ = number of participants in the trial, without considering clusters;m = number of participants in the cluster (i.e., the average number of GPs in the cluster);ICC = intra-cluster correlation (i.e., the correlation among GPs in the cluster).

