#### Statistical methods

All participants will be included in the analysis. This type of analysis is called intention-to-treat and is considered the best way to preserve the effects of randomization [53, 60]. Answers generated by questionnaires and surveys will be analyzed using SPSS Statistical Software (version 24).

T-tests on the difference in cluster means between the intervention and control groups [53] will be assessed for the questionnaires administered to the GPs. Two-tailed P values of less than 0.05 will be considered statistically significant. While the aforementioned t-tests take into account cluster level analysis, individual level analysis is discarded, which can underestimate the power of the analysis and generate misleading conclusions about the intervention [53, 61]. Adjustments can be made to the t-tests in order to account for individual level analysis. Campbell et al. (2000) [61] suggest that the t-test values (i.e., the differences between groups) should be divided by the square root of the design effect (i.e., 1 + (m-1) ICC). Two-tailed P values of less than 0.05 will be considered statistically significant. Individual level analysis will result in a higher significance level, compared with cluster level analysis [61].

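### Delegations are allocated to two arms by a rule that names both simple randomisation and fixed blocks of 3, with no ratio stated, so equal arms are not guaranteed

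*Protocol article*

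**What the plan says.** Under Study setting, the design is fixed as follows: "a cluster randomized controlled trial (RCT) with two arms (i.e., intervention and control) will be conducted". The clusters are delegations: "There are 22 delegations in Tunis and 16 in Sousse, for a total of 38 delegations".

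Under Allocation sequence generation, the aim is given as "A randomization scheme must be generated to randomize the delegations either to the intervention or control group". The method is that a random seed in SAS "will be used to produce simple randomization by fixed blocks of 3", and then "A list of these simple blocks will be used to determine the delegation assignment".

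The article states no allocation ratio, neither 1:1 nor 2:1. It describes one list and mentions no stratum. Under Statistical methods, the arms are compared by t-tests on cluster means with no covariate.

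**The concern.** The block size does not fit the number of arms. A block of 3 can be 2:1 or 1:2 (or 3:0), but never equal. Blocks of 3 would suit a 2:1 trial, but the article neither states nor justifies that ratio. Under Allocation concealment mechanism, all GPs in the included delegations are to be offered the training at some point, so no stated aim calls for one arm to be larger.

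The sentence also gives two names to one procedure. Simple randomisation assigns each delegation independently; blocking constrains the assignments. Two programmers following the text could produce materially different trials.

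The lesser issue is governorate. The Background places the country's only mental health hospital in the capital and psychiatric units in regional hospitals along the coast, so the service context plausibly differs between Tunis and Sousse. With 38 units, an unstratified draw can leave the governorates unevenly spread over the arms, and the t-tests as described would not adjust for that.

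At stake are some efficiency and a reproducible allocation. The allocation cannot be redone once it has been made, and the 38 clusters are all the delegations in the two governorates, so lost efficiency cannot be recovered by adding delegations there.

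**Working it through.** **Inputs.** Two arms; 38 delegations, 22 in Tunis and 16 in Sousse (Study setting). Block size 3 (Allocation sequence generation). 15 GPs per delegation, raised to 19 for 20% attrition (Sample size). Two-sided alpha of 0.05 (Statistical methods).

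**The plan's own figure.** 15 / (1 − 0.20) = 18.75, rounded up to 19; 38 × 19 = 722. This matches Table 1 and does not depend on the allocation rule.

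**Blocks.** 38 = 12 × 3 + 2, so there are 12 complete blocks and the first two places of a thirteenth.

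*Case A: every block has the same 2:1 composition.* Twelve blocks give 24:12. The last two places come from a block with two majority slots and one minority slot. Both are majority slots with probability (2/3)(1/2) = 1/3; otherwise there is one of each.
- 25:13 with probability 2/3 (475:247 GPs at 19 per delegation)
- 26:12 with probability 1/3 (494:228 GPs)

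A split of 24:14 cannot arise here, because it would need two minority places in the last block.

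*Variance relative to 19:19*, with equal variance of cluster means: (1/a + 1/b) / (2/19).
- 25:13: (0.0400 + 0.0769) / 0.1053 = 1.11
- 26:12: (0.0385 + 0.0833) / 0.1053 = 1.16

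In equivalent delegations, 38 / 1.111 = 34.2 and 38 / 1.157 = 32.8.

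*Illustrative power.* Take an effect that would have 80% power at 19:19 (normal approximation, 1.960 + 0.842 = 2.802).
- 25:13: 2.802 / √1.111 − 1.960 = 0.70, power 76%
- 26:12: 2.802 / √1.157 − 1.960 = 0.64, power 74%

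*Case B: each block is 2:1 or 1:2 with probability 1/2 (an assumption).* After 12 blocks the intervention count is 12 + Binomial(12, 1/2). The last two places add 2, 1 or 0 with probabilities 1/6, 2/3 and 1/6.
- P(19:19) = (2/3)(924/4096) + 2 × (1/6)(792/4096) = 0.150 + 0.064 = 0.21
- P(difference of 4 or more delegations) = 0.41
- P(difference of 6 or more) = 0.17
- Possible range: 12:26 to 26:12

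**Governorate without strata.** Suppose the overall split is exactly 19:19. The number of Tunis delegations in the intervention arm is then hypergeometric: P(k) = C(22, k) C(16, 19 − k) / C(38, 19).
- 11:11: 0.26
- 13:9 or worse, either way: 0.32
- 14:8 or worse: 0.10

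**With strata.** 22 and 16 are both even. Drawing 11 of 22 and 8 of 16 gives 11 + 8 = 19 per arm, always (361:361 GPs at 19 per delegation).

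**The case against.** **No 1:1 target is stated, and unequal allocation is valid.** This stands. The fault is that no ratio is given and that the block size fits only a ratio the article does not adopt.

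**The 3 may mean three per arm.** Blocks would then be 3:3, and 38 = 6 × 6 + 2 would end at 19:19 or 20:18. The text does not exclude this, but a block of 3 ordinarily means three units, so the reading is strained. If it was intended, the sentence still has to say so.

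**The power figures have no plan behind them.** This stands. Under Sample size, 0.80 is an input to a sensitivity calculation made after data collection, and estimating the effect size and ICC is itself an aim. The percentages only give a sense of scale.

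**Strata may have been left out of a condensed article.** This stands in part. That there are none is inferred from a single list of blocks, not from an explicit statement, so governorate is secondary. Study setting also describes the two governorates together as having access to the mental health hospital, and no figure links governorate to the outcomes.

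**Stronger readings that the documents do not support.** A reader might infer that 1:1 is impossible. That is true of every complete block, and of the whole trial in case A, but in case B equal arms can occur by chance. A reader might also infer that the t-test fails. It does not need equal arms, and the sensitivity calculation takes the two group sizes as found. Finally, a reader might infer that the result would be confounded by governorate. Chance imbalance under a valid randomisation is covered by the test's error rate and is not systematic bias.

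**Conclusion.** The point holds as a defect in the randomisation rule. The rule combines two methods, states no ratio and uses a block size that cannot balance two arms. The cost is modest: a variance 11% or 16% larger under fixed 2:1 blocks, or about a one-in-five chance of 19:19 if block composition varies. These figures assume that all 38 delegations take part, that cluster means have equal variance, and that 3 is the total block length. The choice between cases A and B is not settled by the text. The governorate figures describe imbalance in counts; how much precision that costs depends on differences in outcome that the documents do not give. The case for changing the rule rests on its contradiction and on the absence of any benefit from unequal arms, more than on the size of the loss. The total of 722 is unaffected.

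**What to change.** Before randomisation, delete the wording on simple randomisation and fixed blocks of 3, and state a 1:1 ratio. All delegations are known in advance and consent precedes randomisation (Recruitment), so no sequential list is needed. Randomise in one step within governorate: draw 11 of the 22 Tunis delegations and 8 of the 16 Sousse delegations for the intervention, with the rest as control. If some delegations do not take part and a stratum is odd in number, state beforehand how the extra one is assigned.

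In the analysis, account for governorate at cluster level, for example by a linear regression of cluster means on arm and governorate in place of the unadjusted t-test.

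The cost is a corrected sentence or two, a few lines of code and a slightly changed analysis. With 38 cluster means, residual degrees of freedom go from 38 − 2 = 36 to 38 − 3 = 35. If unequal allocation was intended, the least that is needed is to state the ratio with its reason, name one method, and use a block size that fits.

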#### Allocation concealment mechanism

All GPs working in the delegations included in this trial will be offered the training, but at varying times. Therefore, it will be impossible to determine which delegation (and thus participating GPs) is assigned to either the intervention or control groups. Psychiatrist-trainers, clinicians responsible for GP recruitment, members of the Ministry of Health in Tunisia, and directors of the delegations included in this trial will not be informed of the allocation.

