#### Eligibility criteria

The group of participants who will be recruited for this trial are GPs working within private or public institutions at the level of primary care in Tunis or Sousse. GPs will be recruited by identified clinicians working to promote continuing medical education in Tunis and Sousse. These clinicians, who work within private or public institutions at the level of primary care, have been selected by members of the Ministry of Health in Tunisia to be a part of this trial, as they have advanced knowledge and skills in the field of mental health, and they are mandated to encourage continuing medical education within their respective delegations. GPs will also be approached by 1 psychiatrist-trainer, as she works closely with GPs within the community.

To be included in the trial, GPs must meet the following eligibility criteria: 1) working within public or private institutions at the level of primary care in Tunis or Sousse; 2) having 5 or more years of clinical experience; 3) dedicating a minimum of 1 h per week to mental health; 4) being part of the *Conseil national de l’ordre des médecins de Tunisie* (CNOM), which is the GP order in Tunisia; and 5) being available when the training is scheduled. GPs will be excluded from the trial if they are retired or on sick leave; work in any other setting than in primary or community-based institutions; or do not dedicate any time to mental health or illness within their given work-week.

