Data will be collected at 4 times. At baseline (T-1, or before the training offered to the intervention group), GPs in both groups will be administered the 5 questionnaires (i.e., socio-demographic, knowledge, attitudes, self-efficacy and mental health practice). Post-intervention group training (T-2), both the intervention and control groups will be administered the same questionnaires, minus the socio-demographic questionnaire. The reason for the administration of the same questionnaires to the control group at T-2 is to account for contamination between groups during the intervention group training, and will serve as the pre-training measure for this group, also a way to maximize our sample. T-2 therefore is also known as the pre-test control group training measure. Post-test control group training (T-3), the control group will be administered the same knowledge, attitude, self-efficacy and mental health practice questionnaires. One year after the completion of the intervention group training (T-4), the groups will be administered the knowledge, attitude, self-efficacy and mental health practice questionnaires to assess whether the results of the training program were maintained over time.

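### Training order is the arm, so the claim that allocation cannot be determined is wrong, and availability and T-1 are not tied to a point before allocation is disclosed

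*Protocol article*

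**What the plan says.** Under Allocation concealment mechanism the article gives its premise, "All GPs working in the delegations included in this trial will be offered the training, but at varying times", and concludes from it that "it will be impossible to determine which delegation (and thus participating GPs) is assigned to either the intervention or control groups". It adds that trainers, recruiting clinicians, Ministry members and "directors of the delegations included in this trial will not be informed of the allocation". GPs are not on that list. The Blinding section describes the Ministry and WHO office members who help implement the programme as blinded to the allocation of delegations, and says randomisation avoids selection bias.

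Data collection and methods fixes the schedule: "At baseline (T-1, or before the training offered to the intervention group), GPs in both groups will be administered the 5 questionnaires". T-2 follows the intervention group's training, is answered by both groups, and precedes the control group's training: "T-2 therefore is also known as the pre-test control group training measure".

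Two further statements bear on selection. Eligibility criteria includes "5) being available when the training is scheduled". Recruitment says that interested GPs are contacted "to obtain written consent before randomization". Statistical methods commits to an intention-to-treat analysis of all participants.

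**The concern.** Staggering the training does not hide the arm when the order of training is what distinguishes the arms. The article also runs together two things: concealment before assignment, which protects against selective recruitment, and blinding after assignment, which protects against biased responses. The design can deliver the first. It cannot deliver the second for the people who attend or give the training. If the sentence stands, the trial will report a protection that it does not have, for outcomes that include subjective self-ratings.

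The availability criterion raises a related question. It refers to a date that depends on the arm, so when it is applied decides whether it is a harmless entry condition or an exclusion made with the allocation known.

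**Working it through.** The claim rests on no figure, so the check is a comparison of sections.

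**Step 1: does varying timing conceal the arm?**

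| Time point or period | Intervention delegations | Control delegations |
|---|---|---|
| T-1 | questionnaires, untrained | questionnaires, untrained |
| T-1 to T-2 | trained | not trained |
| T-2 | questionnaires, trained | questionnaires, untrained |
| T-2 to T-3 | already trained | trained |

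The arm can be read from the second row. The premise that everyone is trained at varying times is true, but the conclusion does not follow from it.

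**Step 2: who can see the second row?**
- GPs: each one knows at T-2 whether he or she has been trained, even without knowing the arm's label.
- Trainers: the Interventions section has three psychiatrists deliver the sessions, so they see which delegations attend first.
- Delegation directors and implementing Ministry and WHO staff: they need not be told the allocation to infer it from the training schedule.

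**Step 3: does it matter for the outcomes?** The Outcomes section names knowledge, attitudes and perceived clinical self-efficacy. T-2 is the time point at which a trained group is compared with an untrained one. Attitudes and self-efficacy are self-ratings, so a GP's awareness of having just been trained can move the answer. Knowledge is measured by a test, where this concern is weaker.

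**Step 4: when is availability settled?** Three statements have to fit together: consent before randomisation, eligibility that depends on the training date, and analysis of all participants. There are two ways to apply the availability criterion.
- Ask before randomisation about both periods. No arm-related exclusion arises and the three statements agree.
- Ask about the delegation's actual date after allocation. Consented GPs could then be removed for arm-specific reasons, against the commitment to analyse everyone.

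The article does not say which applies. According to Recruitment and Implementation, one role obtains consent, generates the sequence and assigns delegations, so no separation of roles is described that would guard this step.

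**Step 5: when is T-1 answered?** It is one common baseline for both groups, fixed relative to the intervention group's training and not relative to disclosure of allocation. It could be answered before or after the arm is known.

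**Scale, on assumed inputs only.** If a share u of consented GPs is removed from an arm, and those removed differ from those retained by d SD, the retained mean shifts by −u × d. The between-arm bias is then (difference in u) × d. With none removed in one arm and 5% to 20% in the other, and d from 0.2 to 0.5 SD:
- smallest: 0.05 × 0.2 = 0.01 SD
- largest: 0.20 × 0.5 = 0.10 SD
- equal removal of similar GPs in both arms: 0

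None of these inputs comes from the article. They show only that the result depends on unequal removal, not on removal as such.

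**The case against.** The strongest reply is that the main selection risk in a cluster trial, recruitment by people who know the arm, is already addressed: consent comes before randomisation, and recruiting clinicians and directors are not informed of allocation. This stands. It confines the selection point to what may happen after consent.

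It can also be said that GPs cannot be blinded to a training course, that the Blinding section does not claim they are, and that a condensed article need not spell out every operational step. The first two are correct, but they do not rescue the statement that the arm cannot be determined, which is a positive claim that the schedule contradicts. The third is fair for the timing of availability and T-1: this is an ambiguity to resolve, not a demonstrated error.

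A reader might go further and infer any of the following. The document does not support them.
- That T-1 itself opens arm-related selection. It is common to both groups and precedes all training, and the timing of a questionnaire does not select participants.
- That availability must be determined after allocation. It could be asked at consent for both periods.
- That every outcome is self-report. The knowledge questionnaire is a test.
- That arm-specific exclusions are planned. No section says so.

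**Conclusion.** The concealment statement is wrong as written, because order of training reveals arm to GPs, trainers and anyone who sees the schedule once training begins. The Blinding statement about implementing Ministry and WHO staff has the same weakness. The consequence is possible expectation bias in self-rated attitudes and self-efficacy at T-2, together with a reported protection that does not exist.

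The second part is conditional. An arm-specific exclusion under the availability criterion, or a baseline answered with arm known, is possible because the article does not place either step before disclosure of allocation. Neither is shown to occur. No size can be derived from the document; the 0.01 to 0.10 SD range rests wholly on assumed, unequal removal. The point warrants correction of the text and of the order of steps. It does not show that the randomised comparison is biased.

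**What to change.** 1. Replace the concealment claim, and the matching claim under Blinding, with a statement that allocation is concealed until consent, eligibility and T-1 are complete for all delegations and the participant list is locked, and that the trial is open to GPs and trainers afterwards.
2. Define the availability criterion as availability for either training period, confirmed before allocation is disclosed.
3. Keep every GP on the locked list in the analysis, including any who later cannot attend.
4. Say that attitude and self-efficacy results will be interpreted as unblinded self-report.

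The cost is mainly wording, plus completing T-1 before disclosure. GPs must be available for two periods, so a few who could attend only one would be ineligible.
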